#### Power Calculations and Sample Size Estimates

The goals of this study are to examine the feasibility, acceptability, and effectiveness of the complex intervention. As observed in previous studies, with respect to the feasibility component, the present study aims to achieve 20% recruitment/consent rate (ie, number of invited GPs who confirm their interest in the study) [19], 75% participation rate (ie, the number of participants allocated to the intervention arm who will receive/complete SBI) [5], and 75% retention or follow-up rate [5].

Based on the recommendations for good practice in pilot studies [32,33], we estimate that 160 patients (attending 16 general practices) will be adequate to calculate the actual recruitment and retention rates (ie, *feasibility*) for a sample of patients recruited in primary care and provide data on *acceptability* of study processes and outcome measures, which will inform a future definitive trial. This pilot study is not powered to determine effectiveness of SBI on reduction of alcohol consumption among problem drug users. The proportion of patients who reduce their alcohol consumption will be used to predict the sample size and length of follow-up for a future definitive RCT.

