**Objective:**

The objective of this study is to determine if a complex intervention including SBI for problem alcohol use among problem drug users is feasible and acceptable in practice. This study also aims to evaluate the effectiveness of the intervention in reducing the proportion of patients with problem alcohol use.

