**Methods:**

Psychosocial intervention for alcohol use among problem drug users (PINTA) is a pilot feasibility study of a complex intervention comprising SBI for problem alcohol use among problem drug users with cluster randomization at the level of general practice, integrated qualitative process evaluation, and involving general practices in two socioeconomically deprived regions.
Practices (N=16) will be eligible to participate if they are registered to prescribe methadone and/or at least 10 patients of the practice are currently receiving addiction treatment. Patient must meet the following inclusion criteria to participate in this study: 18 years of age or older, receiving addiction treatment/care (eg, methadone), or known to be a problem drug user. This study is based on a complex intervention supporting SBI for problem alcohol use among problem drug users (experimental group) compared to an “assessment-only” control group. Control practices will be provided with a delayed intervention after follow-up. Primary outcomes of the study are feasibility and acceptability of the intervention to patients and practitioners. Secondary outcome includes the effectiveness of the intervention on care process (documented rates of SBI) and outcome (proportion of patients with problem alcohol use at the follow-up). A stratified random sampling method will be used to select general practices based on the level of training for providing addiction-related care and geographical area. In this study, general practitioners and practice staff, researchers, and trainers will not be blinded to treatment, but patients and remote randomizers will be unaware of the treatment.

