#### Phase 2: Exploratory Study

A pilot study in addiction clinics showed that SBIs are effective in reducing alcohol consumption among opiate-dependent patients [16]. There is a current proposal to establish the acceptability and effectiveness of the intervention by conducting a feasibility study in primary care.

This protocol reflects the development and piloting phases of the MRC’s “Framework for the design and evaluation of complex interventions to improve health” [20,22]. The present study will provide key parameters regarding the feasibility and acceptability of the intervention to patients and practitioners. As such, this research is essential to inform the design and conduct of a larger cluster randomized controlled trial (RCT).

The specific objectives of the study are as follows. First, this study aims to develop a complex intervention that will enhance SBI for problem alcohol use among problem drug users in primary care. This study will help to establish the practical feasibility and acceptability of complex intervention (1) by conducting a pilot study (with randomization at the level of practice), (2) exploring the feasibility and acceptability of the intervention under study and related research procedures to GPs, practice nurses, and patients, and (3) exploring the fidelity of the interventions as delivered in practice. Finally, we can decide to inform the subsequent design of a definitive cluster RCT by describing the optimum configuration of the complex intervention and by estimating the key parameters in such a trial (ie, practice/patient recruitment and retention rates, intraclass correlation coefficient for primary outcome measures, and the likely effect of intervention under study on these measures).

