### Qualitative Evaluation

A parallel qualitative evaluation will also be conducted with patients and health care professionals.

With regard to health care professionals, open-ended questions will be asked eliciting information on staff attitudes toward alcohol SBI, previous practice of alcohol SBI, preparedness to undertake these activities, the training required to implement SBI, the suitability of each site to provide SBI, and other barriers to effective implementation [34].

With regard to patients, among a 20% purposive sample (estimated N=16) of patients in the intervention practices, we will also explore patients’ satisfaction with and experience of intervention and care related to problem alcohol use in the preceding 3-6 months. Interviews will be done by researcher via telephone, postal questionnaire, or in person. Prior to the interviews, the participant will be informed of the interview purpose, the interview procedure, and the use of the findings. The participant will then be invited to sign an additional consent form and the interview will commence.

Qualitative data analysis will be systematic and organized to easily locate information within the dataset when tracing results, providing examples in context [43]. The qualitative research software Nvivo v8 will be used to facilitate the coding. Thematic analysis will be used to analyze qualitative data. This approach has many benefits for such an interpretive study, as it is a “method for identifying, analyzing, and reporting patterns (themes) within data” [43].

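### The pilot cannot supply the definitive trial's length of follow-up, its effect estimate is too imprecise to size that trial, and the quantity named is not the declared effectiveness outcome

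*Protocol article*

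**What the plan says.** The Power Calculations and Sample Size Estimates section justifies the size on feasibility grounds: "we estimate that 160 patients (attending 16 general practices) will be adequate to calculate the actual recruitment and retention rates". It then states: "This pilot study is not powered to determine effectiveness of SBI on reduction of alcohol consumption among problem drug users". The next sentence reads: "The proportion of patients who reduce their alcohol consumption will be used to predict the sample size and length of follow-up", referring to a future definitive trial.

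The Phase 2: Exploratory Study section lists what the pilot should deliver for that trial: recruitment and retention rates, and the "intraclass correlation coefficient for primary outcome measures, and the likely effect of intervention under study on these measures".

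The abstract names feasibility and acceptability as primary outcomes. Its secondary patient outcome is the proportion with problem alcohol use at follow-up, matching the stated aim: "This study also aims to evaluate the effectiveness of the intervention in reducing the proportion of patients with problem alcohol use". Table 1 lists AUDIT under effectiveness.

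The Timeline section places quantitative data collection at baseline (T1) and at 3 months (T2). The Overview of the Intervention section has control practices give usual care during the study and receive the complex intervention afterwards.

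**The concern.** Two adjacent sentences pull against each other: the study is said to lack power for an effect on drinking, yet a drinking result is to set the size and duration of the next trial. Three separate problems follow.

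- **Length of follow-up.** One post-baseline assessment cannot show whether an effect grows, holds or fades.
- **Precision.** An effect estimated from a small cluster-randomised pilot varies so much by chance that a sample size computed from it is close to arbitrary.
- **Quantity.** Reducing consumption and no longer having problem alcohol use are different events. A patient can cut down and remain a problem drinker.

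Informing a definitive trial is a stated purpose of this pilot. A trial planned this way could be far too small or needlessly large, or could be abandoned because the pilot happened to show nothing.

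**Working it through.** **1. Length of follow-up (no arithmetic needed).** Patient outcomes are measured at T1 and T2 only. After T2 the control practices receive the intervention, so no randomised comparison with an untreated group remains. The period of 3 to 6 months in the Qualitative Evaluation section is the span of experience that interviews explore, not a second outcome assessment.

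**2. Patients available.**
- Planned size: 160 patients in 16 practices, or 160/16 = 10 per practice.
- Intervention arm: "among a 20% purposive sample (estimated N=16) of patients in the intervention practices" gives 16/0.20 = 80 patients, hence 80 per arm. Eight practices per arm is assumed.
- Retained: with the target "75% retention or follow-up rate", 0.75 × 80 = 60 per arm, or 60/8 = 7.5 per practice.

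The article gives no power, effect size or ICC, so there is no power calculation to reproduce.

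**3. Precision of a between-arm difference.** Illustrative rates are 35% (the problem-alcohol-use prevalence cited from the national study) against an assumed 25%. The assumed ICC is 0.05, with a range of 0 to 0.1.
- Design effect: 1 + (7.5 − 1) × ICC = 1.000, 1.325 and 1.650 for ICC 0, 0.05 and 0.1.
- SE = √[(0.35 × 0.65 + 0.25 × 0.75)/60 × design effect] = √[0.415/60 × design effect].

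| ICC | SE (points) | Chance of observing no benefit or worse, true difference 10 |
|---|---|---|
| 0 | 8.3 | 11% |
| 0.05 | 9.6 | 15% |
| 0.1 | 10.7 | 17% |

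At ICC 0.05 the central 95% of observed differences is 10 ± 1.96 × 9.6, or about −9 to +29 points. The chance of observing 20 points or more is also 15%.

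**4. What that does to the sample size.** Patients per arm at 80% power, two-sided 5%, before any design effect: n = (1.96 + 0.84)² × [p₁(1 − p₁) + p₂(1 − p₂)]/d².
- 35% v 15% (20 points): about 70.
- 35% v 25% (10 points): about 326.
- 35% v 30% (5 points): about 1,374.

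The ratio 1,374/70 is about 20. A common design effect leaves that ratio unchanged.

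**5. The same check on the quantity named in the sentence.** The rates above are for problem alcohol use. For the proportion reducing consumption the article gives no figure, so 20% v 35% is assumed. With 60 per arm the 95% CI for the difference is −1 to +31 points (ICC 0) or −3 to +33 (ICC 0.05). By the pooled-variance formula, the total for independent patients at the true 15-point difference is 276. The central 80% of pilot results (control rate held at 20%) would instead imply:
- ICC 0: about 106 to 2,464.
- ICC 0.05: about 96 to 5,370.

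Problem drinking is not an entry criterion. If only problem drinkers were counted, 0.35 × 60 = 21 per arm would remain, with a CI half-width of 26 to 31 points over the rates and ICCs (0 and 0.05) tried.

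**6. What the pilot does estimate usefully.** Retention of 75% in 160 patients has a half-width of 1.96 × √(0.75 × 0.25/160) = 6.7 points, or 8.1 points with design effect 1 + 9 × 0.05 = 1.45. The ICC is weaker: with 16 practices of 7.5 and a true value of 0.05, SE = √[2 × 0.95² × 1.325²/(7.5 × 6.5 × 15)] = 0.066, a 95% range of about −0.08 to 0.18. It should therefore enter planning as a cautious value, not as a point estimate.

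**The case against.** The strongest reply is that the sentence speaks of a proportion, not of a difference between arms. A proportion can enter a sample-size calculation as a planning rate, which is legitimate. Nor does the sentence call it the only input: the Phase 2 section adds recruitment, retention and the ICC. Nothing says that a bare point estimate will be used without its interval, and the calculation itself belongs to a later protocol. AUDIT is collected at both times in both arms, so the declared outcome will be available whatever this sentence names. These points stand and limit the severity. They do not remove the problem: the same Phase 2 list includes the likely effect, no wording confines the proportion to a planning rate, and nothing rescues the prediction of follow-up length.

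Three stronger readings are tempting, and the article does not support them.

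- **That the ICC is promised for the wrong outcomes.** The abstract says "Primary outcomes of the study are feasibility and acceptability of the intervention to patients and practitioners", so a reader might infer that the ICC and effect concern feasibility measures. In the Phase 2 section, however, the parameters listed are those of the definitive trial, and the natural reading is that trial's primary outcomes.
- **That the aims invite an unsupported claim of effectiveness.** The objective is loosely worded, but the sample-size section disclaims power, effectiveness is a secondary outcome, and the Results and Discussion promise only a first indication.
- **That 160 patients is the wrong size.** It is justified for feasibility and acceptability, and nothing here shows it to be inadequate for those.

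**Conclusion.** The point holds and should be fixed, though it is not critical to this trial. That the pilot cannot inform length of follow-up is a fact of the design and rests on no assumption. The imprecision depends on assumed rates, ICC and eight practices per arm, so the exact figures are illustrative: an SE of 8 to 11 points and implied sample sizes differing about 20-fold or more. The conclusion did not change under any of the rates and ICCs tried. The mismatch between reduced consumption and problem alcohol use is real but the smallest part, because the data for the declared outcome are collected anyway. Eligibility, randomisation, data collection and the feasibility results of the pilot are unaffected. The harm would fall on the definitive trial if it were planned as the sentence says.

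**What to change.** In the Power Calculations and Sample Size Estimates section:

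- Delete the reference to length of follow-up.
- State that the definitive trial will be sized on a prespecified minimum important difference in the declared AUDIT-based outcome, the proportion with problem alcohol use at follow-up.
- State that the pilot will supply the control-arm proportion, recruitment, retention, and a cautious value taken from the ICC's confidence interval.
- State that the pilot's effect will be reported only as an estimate with a 95% CI.

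The ICC wording in the Phase 2 section can stay. The cost is a change of wording: the article promises slightly less, and no procedure or data collection changes.

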**Figure 1 figure1:**
[figure not shown]
CONSORT diagram: participant flow and follow-up.

### Intervention

#### Overview

A staggered intervention design will be adopted, whereby participating practices randomized to the intervention arm of the study will be provided with the complex intervention for the duration of the study period, while practices randomized to the control arm of the study will provide usual care to patients for the duration of the study and will be provided with the complex intervention thereafter (ie, delayed intervention). Such an approach was used successfully in our previous cluster randomized controlled study to improve screening for hepatitis C among problem drug users attending general practice in Ireland [25].

#### Control Intervention

All practices (control and intervention arms) will be required to establish a “disease” register of “problem drug users” before the study onset. They will identify potential participants and recruit them for the study. At this stage, participants will be asked to sign an informed consent form. The research team will conduct interviews (telephonic or in person) to determine problem alcohol and other drug use and demographic details at baseline and at 3 months follow-up. Researchers will facilitate data collection (including morbidity and primary/secondary care utilization) from clinical records. Participating practices will be offered €50 per patient recruited to study upon receipt of completed data [34].

We consider the above engagement with practices as close to “usual care” as possible while still allowing evaluation of the complex intervention. To enable the development of a practice register of people with problem drug use, clinical records and prescribing information will be reviewed. For practices who use electronic patient records, an International Classification of Primary Care disease code (P19) will be assigned to patients who meet the criteria of European Monitoring Center for Drugs and Drug Addiction for problem drug use. For practices who use paper records, this register will be developed in a hard copy.

#### Experimental Intervention

A complex intervention will be delivered to practices assigned to the intervention arm at two levels: (1) practice level and (2) patient level.

Interventions that are delivered at practice level include CME/CPD-accredited education delivered both internally (practice-based academic detailing) and externally (seminar), dissemination of clinical guidelines, other resources to facilitate implementation at practice level (eg, contact details/referral information for local services).

All practices will participate in the external education (seminar). Internal education (practice-based academic detailing) will be offered on as-needed basis, depending on practice resources and experience with SBI [35]. Academic detailing and support will be available to practices during the 3 months study period. The number and duration of these visits will be used to predict the level of support for a future definitive RCT.

At patient level, SBI (10-15 minutes) is delivered to patients.

### Data Collection

#### Timeline

At baseline, demographic details and data on primary/secondary outcome measures will be collected by reviewing clinical records and by patients completing study instruments. At follow-up, data will again be collected by reviewing clinical records and by patients completing study instruments. Participants will be invited to complete a follow-up interview with a researcher to include primary/secondary outcome measures. A purposive sample of patients in the “intervention” arm will be interviewed regarding their experience in care for alcohol-related problem in the preceding 3 months.

Quantitative data will be collected at baseline (T1) and at 3 months follow-up (T2) using clinical records (T1, T2), self-/interviewer-administered questionnaires and semistructured interviews (patients, T1, T2), and self-administered questionnaires, including open-ended questions (practitioners, T2).

#### Outcome Measures

Table 1 summarizes the key data being collected during the study.

##### Staff and Organization Measures

Health care professionals at participating practices will be asked to complete a self-administered questionnaire that will elicit data on practice/professional details, experience of training, intervention fidelity (The NIH “Behavior Change Framework” [36]), and Shortened Alcohol and Alcohol Problems Perceptions Questionnaire (SAAPPQ).

##### System Measures

System measures at the examination include the total number of patients screened for alcohol problems (and method of screening), the number of positive screening, and the number of patients receiving any alcohol intervention (including referral). Results of chemical tests for alcohol and drugs (eg, breathalyzer or urine tests) conducted by GPs will be also retrieved using the practice records (T2) to verify self-report measures.

##### Patient Measures

These measures include indirect examination and direct examination. At baseline and follow-up, the study battery will include the following: (1) Alcohol Use Disorders Identification Test (10 items) (AUDIT), (2) Maudsley Addiction Profile (MAP), and (3) Readiness Ruler.

AUDIT developed by the World Health Organization is used to identify a continuum of problem alcohol use [21,38].

MAP is a brief, structured questionnaire for treatment outcome research and measures problems specifically in four areas: substance use, health risk behavior, physical and psychological health, and personal/social functioning [18,39].

Readiness Ruler will assess patient’s motivational state regarding changing their drinking behavior [41].

##### Financial Incentives

Participating practices will be offered €50 per patient to compensate for the extra administration work as in a similar trial [34]. We consider this a conservative level of remuneration given the additional work involved for participating practices [42].

**Table 1 table1:** Primary and secondary outcome measures to be used at the baseline and/or follow-up examinations.

Aim/Target group	Patient measures	Staff and organization measures	System measures
Feasibility	Indirect (review of clinical records): Sociodemographic characteristics and general medical morbidity (ie, clinical records review using a structured instrument developed previously [24]) at baseline	Self-administered baseline questionnaire to include: Practice/professional details Experience of training Adherence to intervention guide/manual assessed with the NIH “Behavior Change Framework” [36] (includes five intervention adherence strategies: intervention design, training procedures, delivery of intervention, receipt of intervention, and enactment of SBI skills) at follow-up Shortened Alcohol and Alcohol Problems Perception Questionnaire (SAAPPQ)	Indirect (review of clinical records): Current and previous practice, with regards to screening and intervention for problem alcohol use among identified problem drug users Numbers of patients who were (1) screened for alcohol, (2) offered a brief intervention, (3) received the brief intervention, and (4) referred to a specialist at follow-up
Acceptability	Patients’ experience of intervention: semistructured interviews at follow-up (via telephone or in person)	Postal survey to include: SAAPPQ [37] at baseline and follow-up Health care professionals’ experience of the intervention: free text in questionnaires at follow-up eliciting information on staff attitudes toward alcohol screening and brief intervention (SBI), previous practice of alcohol SBI, preparedness to undertake these activities, the training required to implement SBI, the suitability of each site to provide SBI [34]	Postal survey examining: perceived barriers or enablers of implementation of SBIs in Ireland
Effectiveness	Direct (interview at baseline and follow-up): AUDIT [38] Other drug use (eg, Maudsley Addiction Profile [39]) Motivation to change risky behavior (eg, Readiness ruler [40])		Indirect (review of clinical records): Results of chemical tests for alcohol and drugs (eg, breathalyzer or urine tests) will be also retrieved using the practice records to verify self-report measures

